## 2. Materials and Methods

This randomized clinical trial was approved by ethics committee of the research institution, Universidade Federal de Pernambuco, under No. 2.449.800, and it complies with the ethical aspects based on Resolution 466/12 of the National Health Council and the Declaration of Helsinki. 

All volunteers will provide written consent after being informed of the study procedures, possible risks and their right to withdraw at any time, with no consequences for any further treatment. The confidentiality of volunteer data will be protected.

According to the recommendations of the CONSORT extension, possible damages will be reported, resulting in the immediate interruption of treatment [33]. The volunteer will be referred to the emergency department of the research institution hospital if a serious adverse event to the treatment is identified, such as functional disability and/or a life threatening outcome.

The dataset will be stored in a locked room in the LACIRTEM lab in password-protected computer files. These data will be disseminated after completion of the study in international peer-reviewed scientific journals and presented at conferences. Positive, negative and inconclusive results will be published in peer-reviewed journals and presented at national and international conferences. In addition, the data will be shared with the volunteers.

### 2.1. Experimental Design and Location

This is a 12-week (3 times a week), single-blind, randomized, controlled clinical trial with three arms (low-frequency WBV associated with ST, G1; WBV sham associated with ST, G1; and control, G3). The study will be developed in the Kinesiotherapy and Manual therapy Laboratory (LACIRTEM) of the Department of Physiotherapy in the Universidade Federal de Pernambuco (UFPE). Figure 1 is a detailed flow chart of the volunteers.

### 2.2. Sampling and Enrollment Strategies

Older adults with DM2 will be selected from a teaching clinic of physiotherapy waiting list, outpatients physical therapy department of a teaching hospital (Hospital das Clínicas—HC), Nucleo de Atenção ao Idoso (NAI) a healthcare center for old people, and Universidade Aberta à Terceira Idade (UNATI), an education service for old people. The sampling will be performed by convenience. Enrollment strategies will include social media advertisements and media relation communication service (Assessoria de comunicação social—ASCOM/UFPE), as well as handouts distributions and lectures. 

In response to first contact, the volunteers will be invited for a full anamnesis and physical exam with an evaluator to assess their eligibility for the study.

### 2.3. Eligibility Criteria

Inclusion: Men and women between 60 and 80 years old with 2 years of clinical diagnosis of DM2 and pre-obesity (25.0–29.9 kg/m^2^) or with obesity class I (30.0–34.9 kg/m^2^) [34], functionally independent, with no severe foot deformity that may require special footwear, other orthopedic deformities, no high risk of falls, no balance disorders, deep venous thrombosis or need for assistive devices for ambulation, preserved cognitive function assessed by Mini-Mental State Examination (MMSE), considering 19 as cutoff point for poor cognitive function [35], and sedentary (0 to 5 points) or poorly engaged in physical active (6 to 11 points) accordingly to the questionnaire of Habitual Physical Activity (HPA) [36].

Exclusion: Change in the subject’s current medication during the study, secondary physical activity during the training program and persistent hypertensive crisis (≥180 × 110 mmHg) or elevated capillary blood glucose (≥300 mg/dL) that prevent the training program completion.

No compliance: Attendance rate lower than 75% of the scheduled sessions, corresponding to 27 sessions. 

### 2.4. Sample Size

The sample size was based on the primary outcome of lower-limb blood flow circulation evaluated by infrared thermographic imaging (ITI). A minimal clinically important difference for skin temperature asymmetry on the knee anterior region is over 0.5 °C [37]. Based on data from a pilot study, two proportions were compared (G1 = 40% and G3 = 10%), considering power of 80% to detect differences between groups and 5% level of significance. The following formula was used:n = [(Z*α*/2 + Zβ)^2^ P(1 − P)]/(P − Po)^2^

According to the calculation in [38], a sample of approximately 15 volunteers per arm would be necessary. We expect a realistic drop-out rate of about 20%; therefore, 17 volunteers are estimated to be enrolled in each group (total of 51 volunteers).

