### 2.7. Outcome Measurements

#### 2.7.1. Primary Outcomes

**Skin temperature**

The thermographic imaging of lower limbs will be captured by FLIR E40bx^®^ camera (FLIR^®^ Company, Wilsonville, Oregon, EUA), with thermal sensibility of 0.5 °C, light emission value of 0.987 and 160 × 120 pixels resolution. The camera will be positioned at a distance of 1 m from the regions of interest with a 90° angle (perpendicular) relative to the camera lens [49].

The volunteers will have fifteen minutes for acclimatization and rest as the body temperature comes into alignment with the room temperature. The test room temperature will be controlled at 18 °C and 23 °C with relative air humidity between 40 and 70% monitored with a precise thermo hygrometer (KT-908). All volunteers will be previously oriented to avoid pain killers or vasoactive drugs, lotions or moisturizing creams on the regions of interest, in addition to caffeine and nicotine in the 4 h before the exam [49].

After the acclimatization period, the thermal images of the interest points will be registered and, subsequently, the mean temperature will be analyzed by the thermographic software provided by the manufacturer (FLIR^®^ Tools). Table 3 shows the six regions of interest [50]. All the photographic images will be collected by one evaluator only with expertise in managing the camera.

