### 2.9. Data Processing and Analysis

All data records will be kept under custody of LACIRTEM lab and an allocation-blind statistician will conduct all analysis using Statistical Package for the Social Science (SPSS, IBM^®^, EUA), version 23.0, with 5% (*p* < 0.05) level of significance.

Sociodemographic, anthropometric and baseline clinical data for both groups will be expressed as the mean and standard deviation for continuous variables, proportions and percentages for nominal variables. The Kruskal–Wallis H test will be used for continuous variables and Chi-square test will be used to associate nominal variables in order to verify homogeneity between baseline data among the groups. 

All analysis will be conducted in accordance with the intention-to-treat method (ITT) using the last observation carried forward (LOCF) method, which inputs baseline data at postintervention for the dropout cases [59]. Missing values due to participants’ nonattendance or withdrawal are expected in clinical trials. Continuous variables with normal distribution will be expressed as mean and standard deviation and the intra-group comparison will be performed by paired *t*-test, and the inter-group comparison by analysis of variance (ANOVA). For nonnormal continuous variables, data will be expressed in median and interquartile intervals (Q25–Q75) and compared within the groups by Wilcoxon test and among the groups by Kruskal–Wallis H test. Size effect will be calculated to support the statistical significance. 

We will also investigate and register the possible adverse events during the treatment protocol. 

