**Figure 2 diagnostics-12-01550-f002:**
[figure not shown]
Placement of markers in the body the volunteer according to the Davis protocol.

**Table 1 diagnostics-12-01550-t001:** Strength training regimens.

Set A	Set B
[figure not shown] Prone Plank Muscles Worked: Abdominal rectum, external oblique, serratus anterior, pectoralis major, tensor fascia lata, quadriceps.	[figure not shown] Prone Plank Muscles Worked: Abdominal rectum, external oblique, serratus anterior, pectoralis major, tensor fascia lata, quadriceps.
[figure not shown] Seated Low Row Muscles Worked: Trapezius, latissimus dorsi, rhomboids, posterior deltoid.	[figure not shown] Dumbbell Shoulder Press Muscles Worked: Anterior deltoid, lateral deltoid, triceps, trapezius, upper chest.
[figure not shown] Lat Pulldown Machines Muscles Worked: Latissimus dorsum, posterior deltoid, lower trapezius, rhomboids.	[figure not shown] Chest Fly Machine Muscles Worked: Pectoralis major, anterior deltoid.
[figure not shown] Upright Cable Row Muscles Worked: Lateral deltoid, trapezius, anterior deltoid, supraspinatus, infraspinatus, minor round.	[figure not shown] Triceps Pushdown Muscles Worked: Triceps, deltoid, forearm.
[figure not shown] Standing Bicep Curl (Cable) Muscles Worked: Biceps, brachialis, brachioradialis, anterior deltoid, forearm.	[figure not shown] Cable Hip Abduction Muscles Worked: Gluteus maximus, gluteus minimus, tensor fascia lata.
[figure not shown] Standing Leg Curl Muscles Worked: Isquiotibiales, gluteos, sural triceps.	[figure not shown] Cable Hip Adduction Muscles Worked: Long adductor, short adductor, magnum, gracilis, pectinous.
[figure not shown] Leg Extension Muscles Worked: Quadriceps, anterior tibialis.	[figure not shown] Standing Calf Raise Muscles Worked: Sural Triceps.

**Table 2 diagnostics-12-01550-t002:** Description of the whole-body vibration (WBV) protocol over 12 weeks.

Weeks	Time per Exercise (s)/Number of WBV Exercise	Frequency (Hz)	Rest Period (s)	WBV Total Time (s)
1–2	30/8	16	30	480
3–4	30/8	18	30	480
5–6	45/8	20	30	720
7–8	45/8	22	30	720
9–10	60/8	24	30	960
11–12	60/8	26	30	960

**Table 3 diagnostics-12-01550-t003:** Regions of interest (ROI) to be analyzed.

[figure not shown]	ROI: Anterior thigh region. Upper limit: groin. Lower limit: horizontal line aligned with the apex of the patella. Shape: ellipse, following the outline of the thigh.

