[figure not shown]	ROI: Posterior thigh region. Upper limit: horizontal line aligned with the line gluteal. Lower limit: horizontal line aligned with the tip of the fibula. Shape: ellipse, following the outline of the thigh.
[figure not shown]	ROI: Anterior leg region. Upper limit: horizontal line aligned with the tip of the fibula. Lower limit: horizontal line above the malleolus. Shape: ellipse, following the outline of the lower leg.
[figure not shown]	ROI: Posterior leg region. Upper limit: horizontal line aligned with the tip of the fibula. Lower limit: horizontal line above the malleolus. Shape: ellipse, following the outline of the lower leg.
[figure not shown]	ROI: Dorsal foot region. Upper limit: horizontal line aligned with the talocrural joint. Lower limit: horizontal line aligned with the metatarsophalangeal joint. Shape: ellipse, following the outline of the foot.
[figure not shown]	ROI: Plantar foot region. Upper limit: horizontal line aligned with the heel tip. Lower limit: horizontal line aligned with the metatarsophalangeal joint. Shape: ellipse, following the outline of the foot.

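### The stated 80% power is for a comparison of two proportions with an undefined event, which matches no primary outcome and no outcome test listed in the article

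*Protocol article*

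**What the plan says.** **Sizing (section 2.4).** The section presents the thermography primary outcome as its basis. The only clinical benchmark is this: "A minimal clinically important difference for skin temperature asymmetry on the knee anterior region", put at more than 0.5 °C. From a pilot study, "two proportions were compared (G1 = 40% and G3 = 10"%), with 80% power and a 5% significance level. The result is about 15 per arm, raised to 17 (51 in total). The event behind the two percentages is not defined. No SD or mean difference is given for temperature, flow velocity or TUG.

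**Outcome (section 2.7.1 and Table 3).** For each region, "the mean temperature will be analyzed by the thermographic software provided by the manufacturer". Table 3 lists six regions: anterior and posterior thigh, anterior and posterior leg, dorsal foot and plantar foot. The two nearest the front of the knee are "ROI: Anterior thigh region. Upper limit: groin. Lower limit: horizontal line aligned with the apex of the patella" and "ROI: Anterior leg region. Upper limit: horizontal line aligned with the tip of the fibula". The other two primary outcomes, arterial flow velocity in cm/s and TUG time, are also continuous.

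**Analysis (section 2.9).** "Continuous variables with normal distribution will be expressed as mean and standard deviation", compared within groups by paired t-test and between groups by ANOVA. Wilcoxon and Kruskal–Wallis are used if the data are not normal. Chi-square is named only for checking baseline homogeneity.

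**The concern.** A power statement is useful only if it refers to the variable and test that will be reported. Here the sizing section and the outcome and analysis sections describe different quantities. Three problems follow.

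- The 80% does not say how likely the trial is to detect an effect on any listed primary outcome.
- The 40% and 10% cannot be converted into a detectable change in mean temperature.
- A reader could apply the 0.5 °C asymmetry threshold to differences in mean temperature, for which the article does not establish it. Asymmetry need not track mean temperature: limbs can warm without their difference changing, or the difference can change while the mean stays put.

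**Working it through.** **1. The plan's own figure.** Section 2.4 prints n = (Zα/2 + Zβ)² P(1 − P)/(P − Po)². With Zα/2 = 1.960 and Zβ = 0.842, (1.960 + 0.842)² = 7.849. With P − Po = 0.40 − 0.10 = 0.30, the denominator is 0.09. P is not defined, so the options are:

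| Value used for P(1 − P) | n per arm |
|---|---|
| Average of 0.40 × 0.60 and 0.10 × 0.90 = 0.165 | 14.4, so 15 |
| Mean rate 0.25: 0.1875 | 16.4, so 17 |
| P = 0.40: 0.24 | 20.9, so 21 |
| P = 0.10: 0.09 | 7.85, so 8 |

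The first row gives the stated 15. The inputs to that figure are two rates and nothing else; no temperature, in mean or SD, enters it.

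**2. Sizing against outcome and analysis.**

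| | Section 2.4 | Sections 2.7.1, 2.9 and Table 3 |
|---|---|---|
| Variable | Proportion with an undefined event, beside an asymmetry threshold | Mean temperature |
| Site | Anterior knee (for the threshold) | Six regions, no separate knee region |
| Scale | Two proportions | Continuous |
| Between-group test | Comparison of proportions | ANOVA or Kruskal–Wallis |

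The imaging method agrees. The variable, site, scale and test do not.

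**3. What 17 per arm supports on the continuous scale.** Section 2.9 carries baseline values forward for dropouts, so all 17 per arm enter the analysis. For two groups, two-sided 5% and 80% power:

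- Normal approximation: d = (1.960 + 0.842) × √(2/17) = 2.802 × 0.343 = 0.96 SD.
- Two-sample t-test (noncentral t): d = 0.99 SD.
- Three-arm ANOVA with 51 participants: f = 0.45.

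With 15 per arm the figures are 1.06 SD (t-test) and f = 0.48.

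**4. In °C, by assumption only.** The document gives no SD. Multiplying 0.991 by an assumed SD gives:

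| Assumed SD (°C) | Detectable difference (°C) |
|---|---|
| 0.5 | 0.50 |
| 0.75 | 0.74 |
| 1.0 | 0.99 |
| 1.5 | 1.49 |

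**5. If a proportion really were the endpoint.** The standard two-sample formula is n = [1.960 × √(2 × 0.25 × 0.75) + 0.842 × √(0.24 + 0.09)]²/0.09 = (1.200 + 0.484)²/0.09 = 31.5, so 32 per arm. At 17 per arm the power for 40% against 10% is about 53% (normal approximation). The printed formula has a single variance term where a two-arm comparison needs two. That is a separate defect, but it matters if the proportion is kept.

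**The case against.** The best defence is that a journal article condenses a fuller plan, and an unseen analysis plan could define an asymmetry or responder variable. That limits the claim to the outcomes and tests listed in this article. It does not remove the claim, because section 2.4 says the size rests on the primary outcome, and the article itself defines that outcome and its tests differently.

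Several stronger readings are tempting but not supported:

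- **That the 40% and 10% count participants with a left-right difference above 0.5 °C.** The two sentences stand next to each other but are not linked. Left-right is only the natural sense of asymmetry; it is not printed. The supportable statement is that the event is undefined.
- **That the knee is not imaged at all.** The anterior thigh ellipse extends to the apex of the patella and so can take in part of the knee. What is missing is a region for the knee itself.
- **That a treatment given to both legs leaves asymmetry unchanged.** This assumes an equal response in both limbs, which no section states.
- **That the camera's stated 0.5 °C sensitivity puts the threshold at its limit.** The specification alone does not set the resolution of a mean over a whole region.
- **That 17 per arm is too few to detect 0.5 °C in mean temperature.** This applies the threshold to a quantity it was not given for, and the answer depends on an SD the document does not contain.

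**Conclusion.** The point holds as a contradiction within the article. The 80% power belongs to a comparison of proportions that section 2.9 does not plan, on an event that section 2.4 does not define, beside a threshold for a variable that section 2.7.1 does not list. None of the three primary outcomes has a power basis in the article.

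The size can be given only in standardised form: about 0.99 SD for a two-group t-test, or f of about 0.45 for the three-arm ANOVA, at 17 per arm, two-sided 5% and 80% power. This assumes approximate normality, equal variances, no adjustment for baseline (section 2.9 describes none) and all 51 participants analysed. Whether a difference of that size is plausible or important in °C cannot be judged from the document.

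**What to change.** Keep 17 per arm and restate section 2.4 for the outcome that is analysed:

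1. Name one mean-skin-temperature summary and one contrast. G1 against G2 is the contrast that tests the hypothesis at the end of the Introduction (the effect of adding WBV to ST); section 2.4 uses G1 against G3.
2. State that 17 per arm gives 80% power at two-sided 5% only for a difference of about 0.99 SD (f of about 0.45 for the three-arm ANOVA).
3. Convert this to °C with the pilot SD if the pilot recorded one, and otherwise over a stated range of assumed SDs. The article reports only two proportions from the pilot, for G1 and G3, so an SD or a G2 arm should not be presumed.
4. Remove the knee-asymmetry threshold as the benchmark for mean temperature.

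Alternatively, if asymmetry or a responder proportion is the intended endpoint, define it as the primary outcome, including the event counted. Add the knee region to Table 3 and plan a matching between-group test of proportions. The sample size would then need recalculating, as step 5 of the working shows.

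The first route costs a short recalculation and some rewording, with no change to recruitment. The stated power becomes less favourable.

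### Section 2.4 sizes a two-group comparison with a one-sample formula, does not reproduce 15 per arm and under-inflates for drop-out; power for 40% vs 10% is about 47–58%, not 80%

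*Protocol article*

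**What the plan says.** Section 2.4 (Sample Size) bases the calculation on the thermography outcome and on pilot data: "two proportions were compared (G1 = 40% and G3 = 10%), considering power of 80% to detect differences between groups", with "5% level of significance". The printed formula multiplies the square of (Zα/2 + Zβ) by P(1 − P) and divides by (P − Po) squared. P and Po are not defined beyond the two percentages. The result is that "a sample of approximately 15 volunteers per arm would be necessary". The allowance for loss follows: "We expect a realistic drop-out rate of about 20%; therefore, 17 volunteers are estimated to be enrolled in each group", which gives 51 in total.

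Two other places bear on how these figures should be read. Section 2.9 (Data Processing and Analysis) keeps drop-outs in an intention-to-treat analysis by carrying their baseline value forward. It compares groups on continuous outcomes by ANOVA or Kruskal–Wallis. Section 2.7.1 analyses mean skin temperature, which is a continuous measure.

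**The concern.** The text describes a comparison between two randomised groups, but the formula has the variance of only one. Leaving out the control arm's sampling error roughly halves the required number. The stated result then fails to follow even from the printed formula, and the step from 15 to 17 does not match a 20% loss. All the inputs are printed in the same section, so this is a contradiction within the text and not detail left out of a condensed article.

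Section 2.4 is the only justification given for 51 participants. A reader who trusts the 80% would take a non-significant result as stronger evidence against the assumed effect than the design can supply.

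**Working it through.** **Inputs (section 2.4).** Rates 0.40 (G1) and 0.10 (G3), difference 0.30; power 80%, z = 0.842; 5% level, two-sided because the formula shows Zα/2, z = 1.960; drop-out 20%; 15 per arm stated, 17 enrolled. (1.960 + 0.842)² = 7.849.

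**Step 1: the plan's own formula.** n = 7.849 × P(1 − P) / 0.30².
- P = 0.40, Po = 0.10: 7.849 × 0.24 / 0.09 = 20.9, so 21.
- P = 0.10, Po = 0.40: 7.849 × 0.09 / 0.09 = 7.8, so 8.

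Neither is 15. Some departures from the printed terms come closer: the average rate 0.25 in the numerator only gives 16.4, a one-sided z with P = 0.40 gives 16.5, and a one-sample arcsine method gives 14.9. Each changes the printed formula and each is still one-sample. How 15 arose cannot be determined from the article.

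**Step 2: two-sample formula, same inputs.**
- Unpooled: 7.849 × (0.24 + 0.09) / 0.09 = 28.8, so 29 per arm.
- Pooled, mean rate 0.25: (1.960 × √(2 × 0.25 × 0.75) + 0.842 × √0.33)² / 0.09 = 31.5, so 32 per arm.

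**Step 3: drop-out.**
- 15 / (1 − 0.20) = 18.75, so 19 per arm and 3 × 19 = 57 in total. Even the cruder 15 × 1.2 gives 18.
- 17 enrolled tolerates 1 − 15/17 = 11.8% loss if 15 are to complete.

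**Step 4: two-sided power for 40% vs 10%.** The unpooled line is Φ(0.30 / √(0.33/n) − 1.960). The chi-square line enumerates all outcomes of the uncorrected test.

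| Method | 15 per arm | 17 per arm |
|---|---|---|
| Pooled normal | 47% | 53% |
| Exact enumeration, chi-square | 51% | 53% |
| Unpooled normal | 52% | 58% |

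**Step 5: effect of the section 2.9 rule.** Carrying baseline forward leaves n at 17 but dilutes the effect. Assume that each drop-out counts as a non-responder and that 20% are lost in each arm. The rates become 0.8 × 0.40 = 0.32 and 0.8 × 0.10 = 0.08. Power at 17 per arm is then 41% (pooled), 42% (chi-square enumeration) or 45% (unpooled).

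**Step 6: the planned continuous analysis.** No SD is printed, so its power cannot be computed. In SD units, and for one pair of arms only, the normal approximation gives a detectable difference of 2.802 × √(2/17) = 0.96 SD at 80% power with 17 per arm. This is before any dilution from drop-out. Converting it to °C needs the SD.

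**The case against.** The strongest reply is that the trial will not test 40% against 10%. Section 2.9 plans ANOVA or Kruskal–Wallis on continuous outcomes, which often carry more information than a responder proportion, so real power could be higher than the figures above. It could also be lower. This stands as a limit on the point: the percentages describe the sizing comparison only. It does not rescue the 80%, which rests on that comparison and on nothing else in the article.

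A second reply is that intention-to-treat with baseline carried forward keeps all 17 per arm. That is correct. A reader might infer that 20% loss leaves 13 or 14 per arm to analyse and quote power at that size, but section 2.9 does not support this: the loss acts through dilution, not through a smaller n. With all 17 counted and no dilution, power is still only 53–58%.

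A reader might also infer that power is about 50% or less throughout. That is too strong, since the values at 17 per arm exceed 50% before dilution. Lower figures, 33% at 15 and 39% at 17, come from Fisher's exact test, which the article does not plan.

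A one-sided test might have been meant, but the printed Zα/2 says otherwise, and one-sided power would be only about 61–66% at 15 to 17 per arm. The method is attributed to a cited source that is not at hand. That may explain where 15 came from, but the printed inputs, formula and result still disagree.

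**Conclusion.** The point holds for section 2.4 as printed. The formula is one-sample, 15 does not follow from it, a two-sample calculation needs about twice as many (29 to 32 per arm), and 17 does not allow for 20% loss on 15. For 40% vs 10%, two-sided 5%, power falls short of the stated 80% by 22 to 33 percentage points (47–58% across 15 to 17 per arm). The 41–45% after drop-out depends on the non-responder assumption and on equal 20% loss in both arms. No conclusion is available about the power of the ANOVA or Kruskal–Wallis analysis. This must be corrected, because a headline design figure is false on the plan's own inputs and restating it is cheap.

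**What to change.** In section 2.4:

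1. Replace the printed formula with the two-sample formula, define its terms, and report that 80% power for 40% vs 10% would need 29 (unpooled) to 32 (pooled) per arm before drop-out.
2. Keep 51 participants, delete the 80% claim, and state power for 40% vs 10% as about 53–58% with 17 per arm. Add that it is lower once 20% drop-out is handled by the section 2.9 rule: about 41–45% if drop-outs count as non-responders, with that assumption written out.
3. Correct the drop-out sentence. Either 15 completers at 20% loss need 19 per arm (57 in total), or 17 enrolled tolerates about 12% loss.
4. Using the pilot SD, if the pilot supplies one, state the difference in the continuous primary outcome detectable with 80% power at 17 per arm, so that the justification matches the analysis in section 2.9.

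The cost is rewording and a less favourable stated power. No extra participants and no change in conduct are needed. Keeping the 80% claim for 40% vs 10% would instead need 32 / 0.8 = 40 per arm (120 in total) by the pooled formula.
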